### Drop-outs

Differences in drop-out rates across treatment arms and baseline characteristics will be analyzed using Mann Whitney U test. Efficacy and safety will be analyzed for all randomized patients (i.e. intent-to-treat ITT). Additionally, we will also examine efficacy for the per-protocol (PP) population. We will examine the difference in dropout rates and missing visits across treatment arms.

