## Packaging, labeling, and handling of investigational products(s)

Both study drugs will be prescribed and marked according to usual practice at the pharmacy. No administration of the drugs will be handled by study personal.

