## Concomitant medications

Medications that are considered necessary for the safety and well-being of the subject can be given at the discretion of the investigator, unless otherwise specified as an exclusion criterion. Concomitant medications are reported in the CRF.

If treatment fails (positive culture for *Candida albicans* and symptoms), rescue medication of vaginal Clotrimazole 200 mg twice per week will be provided in both study groups for the rest of the study period. The regime of Clomitrazole is another established treatment for vulvovaginal *Candida albicans* infection.

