### Secondary endpoints (variables)

1. The secondary endpoint of treatment efficacy is the proportion of women in each group that has negative vaginal cultures for *Candida* albicans at 3 months’ and 6 months’ follow-ups, after end of prophylactic treatment. The cultures will be analyzed as described under 8.1.1.
2. Adverse events will continuously be registered during the study. The participants can fill out any AE in a web based digital weekly diary but also contact the research midwife when needed. AEs will be described and summarized and compared between treatment arms regarding proportion of women with AE.
3. A symptom and examination score (composite index 0-5) will be measured first at baseline/inclusion and then at 3 follow-ups; 1 week after treatment, 3 months’ follow-up after prophylactic treatment and at 6 months’ follow-up. The investigator will ask the participant for common symptoms of RVVC (typical discharge, itching, dryness of the skin/mucosa, burning and pain). Each present symptom will generate 1 point of the composite index (range 0-5). During the gynecological examination performed at inclusion and at each follow-up, typical clinical findings (redness skin/mucosa, typical discharge, dry skin/mucosa, fissures skin/mucosa, visible candida hyfae under the microscope) will be registered in the CRF. Each finding will generate 1 point of the composite index (range 0-5). The proportion of women in each treatment arm with symptom- and examination score >2 for both the will be used for statistical analyses.

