## Reporting and registration of Adverse Events

At each study visit, adverse events (AE) are continuously registered, starting from start of treatment with the investigational products, up to and including 12 weeks after the subject has ended their treatment with the investigational products. All AE that occur during the study and which are observed by the investigator/study midwife or reported by the subject will be registered in the CRF regardless of whether they are related to the investigational product or not. Assessment of causal relationship, severity, and whether the AE is considered to be an SAE or not will be done by the investigator directly in the *CRF*. The subjects can also report AEs in the digital weekly diary or via communication with the investigator/study midwife. At minimum, for each AE/SAE, a description of the event is recorded (diagnosis/symptom if diagnosis is missing), start and stop dates, causal relationship, severity, if the AE is considered to be an SAE or not, measures and outcome. These data will also be reported in the participant’s medical record.

All reported new symptoms in both study groups will be evaluated as a possible AE.

All AE shall be registered in the CRF from start of treatment to 12 weeks after end of prophylactic treatment *as above (section 9.3, Reporting and registration of Adverse Events)*.

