***Statistical methods:***

Analysis for differences over time for treatment efficacy, AEs, symptom- and examination score, impact on vaginal lactobacilli and relapses will be analyzed for all randomized patients (i.e. intent-to-treat ITT). Additionally, we will also examine efficacy for the per-protocol (PP) population. Four time points will be used to study the efficacy (proportion of participants with negative cultures for *Candida albicans*) in each treatment arm (baseline, 1w post-treatment, follow-up 3 and 6 months). We will examine the difference in means, proportions and median values using 95% confidence intervals (CI). The CI interval will be computed using 1) for a proportion in one sample and 2) logistic or multinomial logistic regression analysis.

Differences in baseline characteristics between the CHG and FLZ groups will be analyzed with Chi2 for categorical data, Mann Whitney U test for ordinal data, or t-test for continuous data to examine potential selection bias at randomization. Differences in drop-out rates across treatment arms will also be analyzed using Mann Whitney U test.

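### The safety comparison counts women who never took study drug, and does not separate adverse events that begin after rescue treatment

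*Protocol*

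**What the plan says.** Two places in the Statistics section set the population for safety. Under Drop-outs: "Efficacy and safety will be analyzed for all randomized patients (i.e. intent-to-treat ITT". Under Statistical methods, AEs stand in the list of outcomes that, together with "relapses will be analyzed for all randomized patients (i.e. intent-to-treat ITT". The only second population is for efficacy: "Additionally, we will also examine efficacy for the per-protocol (PP) population". The protocol names no treated set for safety.

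The AE endpoint is a per-woman proportion (Secondary endpoints, section 8.1.2): "AEs will be described and summarized and compared between treatment arms regarding proportion of women with AE". Under Reporting and registration of Adverse Events, registration opens when study drug is started and runs "up to and including 12 weeks after the subject has ended their treatment with the investigational products". Events "will be registered in the CRF regardless of whether they are related to the investigational product or not". A later sentence in that section counts the 12 weeks from the end of prophylactic treatment instead. Neither rule stops the count at rescue.

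The drugs are prescribed and dispensed through pharmacies, and "No administration of the drugs will be handled by study personal" (Packaging, labeling, and handling). After treatment failure, meaning a positive culture with symptoms, "rescue medication of vaginal Clotrimazole 200 mg twice per week will be provided in both study groups for the rest of the study period" (Concomitant medications). Procedures and flow chart gives another route for a positive culture during the prophylactic and observational phases: the same study drug again if it worked without AEs, otherwise an individual choice.

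**The concern.** Two separate features blur what the AE proportion measures.

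The first is the denominator. Women who never start are in the all-randomised set, but on the protocol's wording their AE window never opens. They can only count as women without an AE. The statistical objective is to show that CHG is no worse than FLZ in efficacy and in safety. For a claim of similarity, dilution of both arms is not conservative.

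The second is the numerator. A woman whose first AE starts while she is on clotrimazole is counted in the CHG or FLZ proportion. If failure rates differ between arms, part of the AE difference then reflects efficacy, and the reader cannot tell how much.

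**Working it through.** **Inputs from the protocol.** 30 women per arm; 86% success, so 14% failure, assumed in both arms; margin 30 points, so CHG success at the margin is 86 − 30 = 56% and failure 44%. These come from Sample size calculations. That section's own figure reproduces: n per arm = (1.645 + 1.282)² × 2 × 0.86 × 0.14 / 0.30² = 22.9, so 23 per arm and 46 in total, at one-sided 5% and 90% power. Nothing below changes it.

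**Assumptions not in the protocol.** Non-starters 1 to 3 of 30; true AE risk on study drug 10% to 40%; added AE risk on clotrimazole among rescued women 5% to 30%.

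**1. Non-starters.** Observed proportion = true proportion × (30 − k)/30.
- True 40%: k = 1 gives 0.40 × 29/30 = 38.7%; k = 3 gives 0.40 × 27/30 = 36.0%.
- True 10%: k = 1 gives 9.7%; k = 3 gives 9.0%.
- With k = 3 in both arms, a true 40% against 20% reads as 36% against 18%, so a 20-point difference becomes 18.
- If non-starting is unequal, for example 3 against 0 with a true 40% in both arms, the result is 36% against 40%: a spurious 4 points in favour of the arm with the non-starters.

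**2. Number of women who could be rescued after the one-week culture.**
- Equal failure: 0.14 × 30 = 4.2 per arm.
- At the margin: 0.44 × 30 = 13.2 on CHG against 4.2 on FLZ.

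These are upper figures for those failure rates at that visit, because rescue also needs symptoms. Later failures could add to them, but the protocol is not consistent about what those women receive.

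**3. Effect of rescue on the any-AE proportion.** With true risk b equal in both arms, failure f and added risk r, the observed proportion is b + (1 − b) × f × r.
- f = 14% in both arms: each arm rises by between 0.6 × 0.14 × 0.05 = 0.4 points (b = 40%) and 0.9 × 0.14 × 0.30 = 3.8 points (b = 10%). The difference between arms is 0.
- f = 44% against 14%: at b = 40%, r = 5%, 41.3% − 40.4% = +0.9 points; at b = 10%, r = 30%, 21.9% − 13.8% = +8.1 points. Both count against CHG.

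**4. Precision for comparison.** Half-width of the 95% interval for the AE difference = 1.96 × √(2b(1 − b)/30): 15.2 points at b = 10%, 20.2 at 20%, 24.8 at 40%.

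**5. Would it help to end the main comparison at rescue?** Assume a true risk of 40% over 24 weeks in both arms, constant hazard, and failures censored at week 2. Risk by week 2 = 1 − 0.6^(2/24) = 4.2%.
- CHG at 44% failure: 0.56 × 40% + 0.44 × 4.2% = 24.2%.
- FLZ at 14% failure: 0.86 × 40% + 0.14 × 4.2% = 35.0%.

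That is a spurious 11 points in favour of CHG. With a true risk of 10% the same steps give 6.0% against 8.7%, about 3 points. At 40% risk this bias is larger than the largest one in step 3, and it favours the arm that fails more.

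**The case against.** The strongest reply has four parts.

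- **The all-randomised set does not cause the mixing with rescue.** A treated set classed by first drug received would keep every rescued woman in the same arm with the same events. This stands. The safety set cures only the non-starter problem; the rescue question needs its own table.
- **Attribution is already handled.** Assessment of causal relationship has the investigator judge each AE against the investigational product, and its lowest category covers events explained by other medications. AE dates and concomitant medications are recorded. This stands for causality, so a reader who infers that clotrimazole effects would be attributed to CHG or FLZ goes too far. It does not help the stated endpoint, which is any AE regardless of relation.
- **Non-starting is speculative.** No rate is given, and pharmacy supply does not show that it happens; compliance is followed by diary and at visits. This stands as to size. The mismatch between denominator and AE window is nevertheless in the text.
- **The SAP may hold a suitable table.** It is listed as an attachment and is not shown. A split before and after rescue could well be there. A treated set as the main safety population could not, without contradicting what the protocol states twice.

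A reader might also infer that rescue mixing pulls the arms together and so helps CHG. The protocol's figures do not support that: the mixing is balanced at equal failure and counts against CHG if CHG fails more. Nor does the share of follow-up time spent on clotrimazole measure the problem, since the endpoint counts women, not person-time. The protocol does not say that study drug stops when clotrimazole is given, and its two routes after a positive culture differ.

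**Conclusion.** The point holds in limited form and is minor. The protocol sets safety as an all-randomised analysis while opening the AE window only at the start of treatment, so non-starters can only dilute. The size is about 1 to 4 percentage points at a 40% AE rate, if 1 to 3 of 30 women never start.

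Separately, first AEs after rescue count in the randomised arm. This gives no spurious difference at equal failure, and about 1 to 8 points against CHG if CHG fails at the margin, given an added AE risk of 5% to 30% on clotrimazole. Both effects lie well inside an interval half-width of about 15 to 25 points.

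A reader might conclude that the main AE comparison should stop at rescue. It should not: under the assumptions in step 5 that would favour the arm that fails more by about 3 to 11 points.

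**What to change.** - Under Statistical methods and Drop-outs, take safety out of the all-randomised statement. Define a safety set of women who took at least one dose, analysed by the study drug actually taken, over the full AE window. Keep the all-randomised table as supportive. State how a woman with no diary entry and no follow-up visit is classed.
- Add a supportive table that splits AEs by onset before or after the start of rescue or other antifungal treatment, with time at risk shown per arm. Do not make the pre-rescue period the main comparison.
- Reconcile Procedures and flow chart with Concomitant medications on what follows a positive culture. Reconcile also the two end dates for AE registration, which can differ for a woman whose study drug ends early.

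The cost is a change of wording and one or two extra tables. Compliance, AE start dates and concomitant medications are already collected, and the sample size is unaffected.

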## Adjustment of significance and confidence interval

For the secondary outcomes, we adjust for the rate of Type I errors by adjusting the p-values by controlling for the false discovery rate (the proportion of Type I errors in all significant findings) among all secondary outcomes examined.

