## Primary objective

To analyze if daily vaginal application of 8 ml of Hibitane® for one week and thereafter once a week for another 11 consecutive weeks is at least as effective as fluconazole 150 mg capsules every third day for the first three doses and thereafter 150 mg once a week for another 11 consecutive weeks regarding treatment- and prophylactic efficacy for recurrent vulvovaginal *Candida albicans* infection*.*

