## Primary endpoint (variable)

The proportion of women in each group that has negative vaginal cultures for *Candida albicans* 1 week after active treatment.

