## Overall study design

The study is a 6 months clinical Phase II trial to compare if 1% chlorhexidine gluconate vaginal cream (Hibitane®) is at least as effective and safe as fluconazole (reference treatment) for culture-verified recurrent vulvovaginal candidiasis. The study is a randomized open non-inferiority trial with parallel treatment groups. The trial is not possible to blind for neither participants nor investigators due to the differences between study treatments. There is low risk of bias since the primary outcome variable is objective (negative vaginal culture for *Candida albicans*).

The rational for the study is to find an alternative treatment to fluconazole for RVVC with high tolerability and without cytotoxic effect on epithelial cells and negative impact on the vaginal microbes.

The participants will be randomization to;

- Investigational medication with Hibitane® vaginal cream 8 ml every night for a week and then prophylactic treatment with 8 ml/week for another 11 weeks

or

- Reference treatment with Fluconazole® 150 mg (oral capsule) every 3 days for the first 3 doses, then prophylactic treatment with 150 mg/week for another 11 weeks

Please see section 7 for more details on randomization and study treatments.

Figure 1 Study design

| **Visit** | **1** | **2** | **3** | **4** | **5** |
| --- | --- | --- | --- | --- | --- |
|  |  | CHG | Chlorhexidine gluconate  vaginal application  8 ml/w, 11 w | |  |
|  |  | 8 ml/day,1 w  R |  |  | N=30 |
|  |  |  | Fluconazole  oral capsules  150 mg/w, 11 w | |  |
|  |  | FLZ  150 mg/day,1w |  |  | N=30 |
| **Week:** | **-1** | **0** | **1** | **12** | **24** |
|  | Screening | Inclusion/  Baseline  Randomization | Follow-up | Follow-up | Follow-up and end of treatment |

##

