## Methods for measurement of endpoints (variables) for clinical safety

Two of the secondary endpoints are used for clinical safety;

1. Adverse events will continuously be registered during the study. The participants can fill out any AE in a web based digital diary and also contact the research midwife when needed. AEs will be registered in the CRF. AEs will be analyzed as proportion of women with AE and compared across study arma. For more details, see section 9.
2. Possible toxic effects on the vaginal cells after CHG treatment will be analyzed in vaginal biopsies described under 8.1.2. The analysis will focus on injuries of the epithelial lining and increase of inflammatory and immunological markers (antimicrobial peptides, cytokines, kemokins, CIDAMP). The biopsies will be taken at inclusion and at 3 months’ follow-up, when the prophylactic phase of the study is completed. Biopsies from participants allocated to FLZ will serve as controls.

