## Statistical analyses

### Statistical methods

***Objective:*** The aim of this study is to analyze whether vaginal chlorhexidine gluconate (CHG) is at least as effective and safe as oral fluconazole (FLZ) as treatment and prophylaxis for recurrent vulvovaginal candidiasis.

***Study design:*** Randomized controlled non-inferior trial with 60 women randomly assigned to either vaginal chlorhexidine gluconate (N=30) or oral fluconazole (N=30). Baseline plus 3 follow-up visits (baseline/inclusion, 1 week, 3 months and 6 months) are planned.

***Primary outcome****:* Proportion of women with negative cultures for *Candida albicans* 1week post-treatment.

***Secondary outcomes****:*

- Negative cultures for *Candida albicans* at 3 months’ and 6 months’ follow-ups, after end of prophylactic treatment.
- Analysis of proportion of women with adverse events (AE). The AEs will also be reported in descriptive terms and summarized for each treatment arm.
- Proportion of women with symptom score > 2. Each symptom of typical discharge, itching, dryness of the skin/mucosa, burning and pain will generate 1 point of a composite index (range 0-5).
- Proportion of women with examination score >2. Each finding of redness skin/mucosa, typical discharge, dry skin/mucosa, fissures skin/mucosa, visible candida hyphae in the microscope will generate 1 point of a composite index (range 0-5).
- Proportion of women with reduced vaginal lactobacilli content in vaginal smears measured by a semi-quantitative method as normal or reduced quantity.
- Proportion of women with relapse of *Candida albicans* infection between end of treatment and end of prophylactic treatment (1week post treatment to 3 months’ follow-up) and between 3- and 6 months’ follow-up after end of prophylactic treatment.
- Proportion of women with possible toxic effect on the vaginal epithelium, defined as disruption and/or inflammation of the epithelial lining, analyzed from vaginal biopsies before and after treatment and prophylaxis.
- Further analysis of mucosa inflammatory mechanism and biofilm formation during and after treatment and prophylaxis, analyzed from vaginal biopsies. The methods for these *in vitro* exploratory analyses are not yet decided on.

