## Sample size calculations

The sample size and calculated power for the primary outcome of negative cultures for *Candida albicans* is based on data in Alvendal et al. Acta Obstet Gynecol Scand. 2017. In that study there was 100% positive cultures for *Candida albicans* before routine treatment with fluconazole for RVVC. After fluconazole treatment, 14% participants were still culture positive, with 86% success rate of primary outcome. Using the presumption: α= 5% β= 90%, success for routine FLZ treatment= 86%, success for experimental treatment with CHG in the current study= 86% with non-inferiority limit= 30%, 46 participants are needed (23 in each group) to achieve a power of 90 % not to exclude an effect-size of 30%. 60 participants will be included in case of drop-outs. All test will be performed at the 5% significance level.

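### The no-worse claim covers prophylaxis and safety, but only the 1-week culture has a non-inferiority test, and the FDR rule makes a deficit or harm harder to flag

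*Protocol*

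**What the plan says.** **The aim.** The Primary objective (4.1) describes both the first week and the 11 weekly doses that follow, and asks whether chlorhexidine is at least as effective "regarding treatment- and prophylactic efficacy for recurrent vulvovaginal" *C. albicans* infection. Section 10.2.1 asks whether it "is at least as effective and safe as oral fluconazole (FLZ) as treatment and prophylaxis for recurrent vulvovaginal candidiasis". Overall study design likewise says "is at least as effective and safe as fluconazole (reference treatment) for culture-verified recurrent vulvovaginal candidiasis" and calls the trial non-inferiority.

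**The test.** The primary endpoint is negative culture "1 week after active treatment". Section 10.4 opens with "The sample size and calculated power for the primary outcome of negative cultures for" *C. albicans* and gives the only margin in the protocol, "non-inferiority limit= 30" percent.

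**Everything else.** Culture at 3 and 6 months, relapse, adverse events, symptom and examination scores, lactobacilli and epithelial toxicity are secondary. Section 10.2.1 analyses them for differences and plans 95% confidence intervals. Section 10.3 adjusts their p-values by "controlling for the false discovery rate (the proportion of Type I errors in all significant findings) among all secondary outcomes examined". Section 8.2 states that "Two of the secondary endpoints are used for clinical safety"; these are adverse events and epithelial toxicity, so both fall inside that family.

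**The concern.** There are two linked problems, both in what the protocol itself fixes.

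1. **The objective is wider than its endpoint.** Prophylactic efficacy is part of the primary objective, yet a culture 1 week after active treatment cannot show whether weekly dosing prevents recurrence. The outcomes that can (3-month culture and relapse) carry no non-inferiority criterion.

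2. **The multiplicity rule points the wrong way for harm.** FDR adjustment can leave a p-value unchanged or raise it, never lower it. That is prudent when a significant difference is the success claimed. In this trial the Synopsis hopes for little impact on lactobacilli, high tolerability and no cytotoxicity. For those outcomes a significant difference is the warning, and the rule makes the warning rarer.

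At stake is a report in which a poorly powered, adjusted, non-significant comparison is taken as support for being at least as effective as prophylaxis, or at least as safe.

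**Working it through.** **1. The plan's own figure.** Inputs from 10.4: success 86% in both arms, margin 0.30, power 90%, α 5%.

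n per arm = (z₁₋α + z₁₋β)² × 2p(1−p) / margin² = (1.645 + 1.282)² × 2 × 0.86 × 0.14 / 0.09 = 22.9, so 23 per arm and 46 in total. The stated size reproduces with α taken as one-sided 5%. It applies to the 1-week culture alone.

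**2. Assumptions for the secondary outcomes.** The protocol gives no event rates for them and names no FDR procedure. I assume:
- 30 per arm (all randomized women), two-sided Fisher exact test, Benjamini-Hochberg adjustment;
- 8 tests if there is one per listed secondary endpoint;
- 15 tests if the visits are counted: culture 2, adverse events 1, symptom score 3, examination score 3, lactobacilli 3, relapse 2, toxicity 1;
- a single real signal, which then has to reach about 0.05/8 = 0.00625 or 0.05/15 = 0.0033.

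**3. Exact results**, summing binomial probabilities over all tables with p at or below the threshold:

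| Assumed truth | Quantity | Unadjusted | 8 tests | 15 tests |
|---|---|---|---|---|
| Adverse events 40% vs 10% | power | 0.705 | 0.396 | 0.299 |
| 3-month clearance 50% vs 70% | P(non-significant) | 0.741 | 0.922 | 0.946 |

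**4. One data set.** Adverse events in 12/30 versus 3/30: difference 0.30, SE = √(0.4×0.6/30 + 0.1×0.9/30) = 0.105, 95% CI 0.30 ± 1.96 × 0.105, or about 9 to 51 points. Fisher p = 0.0153. As the lone signal it becomes 8 × 0.0153 = 0.12 or 15 × 0.0153 = 0.23. The interval excludes zero while the adjusted p-value is non-significant.

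**5. Sensitivity.**
- *Test used.* With a chi-square test in place of Fisher, adverse-event power is 80% unadjusted and 50% at 0.05/8. The clearance deficit is missed 65% and 88% of the time.
- *Several outcomes differing together.* When 4 of 8 or 7 of 15 correlated outcomes differ by 40% versus 10%, simulated power after adjustment is about 51% and 49%, against 40% and 30% for a lone signal. For 50% versus 70% the relief is small: about 89-92% are still missed.

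**6. Could week 12 carry a non-inferiority test?** Power with a 95% CI, no true difference and a 30-point margin is Φ(0.30/√(2p(1−p)/30) − 1.96). At a rate of 86% this is 92%, at 70% it is 72%, and at 50% it is 64%. At a 20-point margin it is 61%, 39% and 34%.

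**The case against.** - **The protocol never equates non-significance with non-inferiority.** This is true. A reader might infer that weak data will be reported as at least as effective and safe. No section says so; the plan only leaves that reading open.
- **Confidence intervals are already planned.** Section 10.2.1 provides 95% intervals for differences, section 10.3 adjusts only p-values, and adverse events will also be described by arm. A 20-point deficit would therefore be visible with a wide interval. This stands as partial mitigation. What remains is that no rule says how to read the intervals, and an adjusted p-value sits beside them.
- **Secondary margins may be in the SAP.** They may, and a missing secondary margin alone is not a finding. The point rests on what the protocol states: an objective broader than its endpoint, and an FDR family that takes in every secondary outcome, safety included.
- **The figures blame adjustment for small numbers.** In part this is right. The 50% versus 70% deficit is missed 74% of the time with no adjustment, so sample size is the main cause there. The lone signal is also the least favourable case for Benjamini-Hochberg. A reader might take 30-40% power as the typical result; it is a lower bound under the stated assumptions.

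**Conclusion.** The point holds in limited form. The primary objective and the aim extend a no-worse claim to prophylaxis and safety, while the protocol provides a non-inferiority criterion only for the 1-week culture. Separately, the rule in 10.3 makes real harm or a real prophylaxis deficit harder to flag.

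For adverse events of 40% versus 10%, adjustment lowers power from 71% to 30-40% in the worst case and to about 50% if several outcomes move together. For a 20-point prophylaxis deficit the adjustment adds to a miss rate that is already high. All of this rests on assumed rates, an assumed count of 8 to 15 tests and an assumed FDR procedure.

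The documents do not show that the sponsor intends to read non-significance as equivalence, nor that adjustment is the main reason a prophylaxis deficit would be missed. The matter should be corrected, but it does not undermine the 1-week primary comparison.

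**What to change.** **Section 10.3:** take adverse events, epithelial toxicity and lactobacilli out of the FDR family. Report them as unadjusted risk differences with the 95% confidence intervals already planned.

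**Sections 4.1 and 10.2:** limit the confirmatory non-inferiority claim to the 1-week culture. Label the 3- and 6-month culture and relapse outcomes as estimation with confidence intervals. State that a non-significant secondary p-value supports no claim of equal efficacy or equal safety. The aim should be worded to match wherever it is repeated (Synopsis, Overall study design).

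**Not recommended:** adding a formal week-12 non-inferiority test. Its margin would be debatable, and 30 per arm gives only about 64-72% power at 30 points if clearance is 50-70%.

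**Cost:** wording only, with no added women, visits or measurements. The price is some chance safety flags from unadjusted comparisons, and a narrower headline claim.
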